### Study population

The study population consisted of people with MD aged between 18 and 75 years living in a SHO in the Flanders region (Belgium). There are 42 SHOs in the Flanders region, including 2662 approved places [23]. Exclusion criteria included people aged <18 or older than 75 years, having a gastric ring or pacemaker placed, having cognitive impairments (assessed by the mental health professionals) compromising the understanding of the psycho-educational and behavioral sessions of the health promotion intervention.

### Development of the materials

The theoretical framework of the intervention was developed using elements of several theories including the social-cognitive theory [24], the self-determination theory [25], and the control theory [26]. The health promotion intervention was developed using the mediating variable approach including the mediating variables knowledge, skills, self-efficacy and motivation [24,25]. A schematic overview of the theoretical framework can be found in Figure 2. Knowledge is a necessary component of behavior change [24]. For example, how to select appropriate food portion sizes, how to distinguish between sedentary and moderate or vigorous physical activities. Behavior-specific skills are those specifically related to the targeted behavior [27]. For example, how to interpret the level of physical shape by measuring the pulse rate. Self-regulatory skills include goal setting and problem solving [27]. Self-efficacy is confidence in one’s ability to successfully perform a task or behavior and is influenced in two ways: personal success and observing others successfully perform the behavior [24]. Two types of motivation can be distinguished. People can be motivated because they value an activity either from a sense of personal commitment or because there is strong external motivation and support [25].

**Figure 2 F2:**
[figure not shown]
Theoretical framework of the health promotion intervention targeting physical activity and healthy eating.

The staff manual was developed based on the manual ‘Health promotion on well-balanced eating and healthy physical activity’ developed by the Flemish Institute of Health Promotion and Disease Prevention [28]. As the target population of this manual is the general population, some adjustments were made to focus especially on the lifestyle behavior of our target population (for example how to choose a more healthy lifestyle despite the presence of barriers associated with the MD). The manual was built around ten themes focusing on PA and healthy eating: 1) PA and healthy eating: Introduction, 2) Awareness of the consumption of fat and fibres, 3) A healthy lifestyle: advantages and barriers, 4) The food triangle, 5) Using the food triangle throughout the day, 6) Label reading, 7) The influence of the environment & Budget issues, 8) & 9) Physical activity, 10) A quiz regarding PA and healthy eating.

### Study duration and intervention components

The study period consists of an intervention period of 10 weeks followed by a post-intervention period of six months. In addition to treatment as usual, the intervention groups (n = 14) receive the 10-week health promotion program targeting PA and healthy eating. In the intervention group the following intervention components are offered:

· Psycho-educational and behavioral group sessions

This part of the program consists of 10 group sessions in a 10-week period and includes discussions on PA and healthy eating, problem solving, written exercises, quizzes and plans to increase PA levels and to stimulate a more healthy eating behavior. All participants in the intervention group receive the same information in the same format. The program is delivered by the mental health professionals working in the intervention SHOs.

· Supervised exercise

In the same 10-weeks period a weekly 30-minutes supervised walking session is organized. These sessions are also led by one or more mental health professionals.

· Individual counseling

During the 10-week intervention period, all participants in the intervention group receive individual support from the mental health professionals (for example motivation to persist, discussing of experiences).

### Implementation of the intervention

The manager of each SHO in the intervention group was asked to discuss with their team of mental health professionals the selection of one or two persons, who would serve as contact person with the research team and who would be responsible for the sessions. Every intervention SHO was visited by the same researcher. The aim of this visit was to instruct the mental health professionals who would lead and supervise the sessions. Preferably, also other staff members were present during this training session. During the study period, it is possible to contact one of the researchers by phone or e-mail. If necessary, visits of one of the researchers to the SHO will also be possible.

### Evaluation of the intervention

At the end of the study period, a process evaluation of the health promotion program will be organized for all participating SHOs in the intervention group. This evaluation will consist of a questionnaire with both closed and open-ended questions including topics on experiences, advantages and disadvantages of the program, lessons learned, and suggestions for further research.

### Sample size calculation

The sample size calculation is based on an average change of the primary outcome body weight of 3.5 kg between the intervention and the control group at the end of the study. This change is based on the results of a previous literature review performed by the research team on the effectiveness and cost-effectiveness of lifestyle interventions on PA and eating habits in people with MD [12]. Cluster randomized trials require larger sample sizes than the individually randomized design. This can be explained by the fact that observations on individuals in the same cluster tend to be correlated, and so the effective sample size is less than the total number of individual participants. This reduction in effective sample size and the degree of correlation within clusters is known as the intraclass correlation coefficient (ICC) [20,29]. As no ICC for this kind of intervention in people with MD was found in the literature, an assumption was made by multiplying the sample size with a design factor of 1.5. A sample size of 371 participants in each group would provide a sample large enough to detect a difference in mean body weight change of 3.5 kg across the two groups with 80% power at a significance level of 0.05.

### Data collection and outcome measurements

#### Sociodemographics

Participants will be asked to complete a questionnaire on sociodemographics including sex, age, duration of stay in sheltered housing, marital status, occupational status, contacts with relatives, tobacco and alcohol use, and medication use.

#### Primary outcome measures

The primary outcomes of the study consists of changes in body weight, BMI, WC and fat mass. Body weight is measured in all participants wearing light clothing without shoes by a member of the research team using a TANITA BC-420 SMA digital weighing scale (TANITA, Tokyo, Japan). A member of the research team measures height in a standardized way using a Seca 225 stadiometer (Seca GmbH & KG, Hamburg, Germany). The BMI is calculated by dividing the body weight in kilograms by the square of the height in meters. WC is measured with a Seca 200 tape (Seca GmbH & KG, Hamburg, Germany) by one of the researchers according to the guidelines described in the National Heart, Lung, and Blood Institute report ‘Clinical guidelines on the identification, evaluation, and treatment of overweight and obesity in adults. The evidence report’ [30]. The calculation of the fat mass occurs using the TANITA BC-420 SMA digital weighing scale (TANITA, Tokyo, Japan). This occurs at the same time as the weight assessment. Both the stadiometer and the digital weighing scale were placed on a flat surface to assure correct measurement of height, body weight, and fat mass.

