### Study design and setting

The design consisted of a cluster preference randomized controlled trial. An overview of the study design can be found in Figure 1. The study was conducted in sheltered housing organisations (SHOs) in the Flanders region (Belgium) with the SHOs as the unit of randomization. In SHOs, support on several domains (e.g. psychological, domestically, occupational, relational) is offered to the patients. In this type of health care service, patients are living alone in a studio or apartment or together with other patients in ‘community houses’. For this reason, cluster randomization was appropriate. Individual randomization at the level of the individual patient would decisively cause contamination bias due to the risk of participants in the intervention and control group living together. Cluster randomization to the intervention or control group therefore occurred at the level of the SHOs.

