**Figure 1 F1:**
[figure not shown]
Health promotion intervention: Study design.

Mental health professionals working in the intervention SHOs were asked to lead and to support the health promotion intervention. This implied a significant involvement and workload above their usual workload. Also, as mentioned before, centers being assigned to a non-preferred intervention arm could be disappointed, which may reduce their interest to participate in the study [12,13]. Moreover, a substantial risk of non-participation was also assumed based on the results of previous qualitative research indicating that lack of time due to the high workload in the daily care of patients is a common barrier for mental health professionals to engage in health promotion programs [21,22]. Consequently, it appeared to be necessary to provide a detailed explanation about the expectations when serving as an intervention SHO. For this reason, preference randomization appears to be appropriate.

An invitation letter and response form with a self-addressed postage envelope was sent to the managers of all SHOs in the Flanders region. They were asked if they were interested to participate in the study having (i) no preference to serve as intervention or control group and to be randomized or, (ii) a preference to serve as intervention group (see a detailed description of the intervention below) or, (iii) a preference to serve as control group. A concise explanation of the aim of the study and of the expectations and content when participating as intervention group was included in the letter. If necessary, a second mailing was foreseen. If a SHO was not prepared to participate, they were asked to report the reason for non-participation.

Subsequently, based on the responses, SHOs were either assigned to the intervention or control group according to their preference or randomly assigned to the intervention or control group when they expressed no preference. Randomization occurred by an external person not involved in the study. Finally, the patients living in the intervention and control SHOs received both written and oral information about the study. The written information consisted of a detailed explanation about the study and an informed consent.

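### Waist circumference, a tape-read primary outcome, is measured by the research team that also trains and supports the intervention SHOs, so follow-up readings need simple protection against knowledge of the arm

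*Protocol article*

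**What the plan says.** Under Primary outcome measures, the protocol article states: "The primary outcomes of the study consists of changes in body weight, BMI, WC and fat mass". Body weight and fat mass come from a digital scale, and BMI is computed from scale weight and measured height. WC is the only one of the four that is itself a hand reading: "WC is measured with a Seca 200 tape (Seca GmbH & KG, Hamburg, Germany) by one of the researchers". The safeguard stated for it is that the reading is taken "according to the guidelines described in the National Heart, Lung, and Blood Institute report".

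Under Implementation of the intervention, the research team also has a role in the intervention arm: "Every intervention SHO was visited by the same researcher". The purpose is given next: "The aim of this visit was to instruct the mental health professionals who would lead and supervise the sessions". During the study, SHO staff can reach a researcher by phone or e-mail, and "If necessary, visits of one of the researchers to the SHO will also be possible".

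Allocation is by site. Study design and setting says: "Cluster randomization to the intervention or control group therefore occurred at the level of the SHOs". Baseline study population characteristics reports that 14 SHOs preferred the intervention and 5 preferred control, so 19 of 25 took the arm they asked for and 6 were randomised. Independence from the study is described for one step, the random allocation: "Randomization occurred by an external person not involved in the study". The article describes no comparable arrangement for outcome measurement.

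**The concern.** A researcher who arrives at an SHO to measure its residents will in practice know its arm. The allocation covers the whole site, and the team has itself instructed the staff at every intervention site. A tape reading depends on where the tape sits and how tightly it is drawn, so it leaves more room for expectation than a digital display.

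A small shift at follow-up in one arm goes straight into the estimated difference in change, and a larger sample does not reduce it. WC has the same primary status as weight. The Data analysis section sets a single threshold of P ≤ 0.05 and gives no rule for a result in which WC alone is positive. The Discussion also presents WC and waist-hip ratio as better than BMI for estimating future cardiovascular risk, so a WC-only result could be given real weight.

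**Working it through.** The plan gives no target effect and no SD of change for WC, so it has no WC figure to reproduce. Its sample size concerns body weight only. The check asks what a given reading bias would do to the WC test.

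**Inputs from the article**
- Participants with baseline data: 201 intervention, 83 control (Tables 1 and 2).
- Design factor for clustering: 1.5 (Sample size calculation).
- Significance level: 0.05 (Data analysis). The sidedness is not stated, and two-sided is assumed here.
- Baseline WC: mean 105.9 cm, SD 16.1 cm (Table 2).

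**Assumptions**
- SD of WC change: 4 to 7 cm, with 8 cm and the baseline SD of 16.1 cm as wider cases.
- Shift b at follow-up in one arm only: 0.5 or 1 cm. A shift of 1 cm is 1/105.9, or about 1%, of the mean baseline WC.
- No true effect and no attrition.

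**Which biases matter.** Let o be an assessor's constant offset and b a shift at follow-up caused by knowing the arm. The measured change is (true follow-up + o + b) − (true baseline + o) = true change + b. The offset cancels and b does not. If the assessor changes from offset o1 to o2 in one arm only, that arm gains o2 − o1, which does not cancel either.

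**Standard error of the difference in change**

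SE = SD × √(1/201 + 1/83) × √1.5 = SD × 0.1305 × 1.2247 = SD × 0.1598

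**Probability of P ≤ 0.05 with no true effect**

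Φ(b/SE − 1.96) + Φ(−b/SE − 1.96)

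For SD 5 and b = 1: SE = 0.80 and b/SE = 1.25, so Φ(−0.71) + Φ(−3.21) = 0.239 + 0.001 = 0.240.

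| SD of change (cm) | SE (cm) | b = 0 | b = 0.5 cm | b = 1 cm |
|---|---|---|---|---|
| 4 | 0.64 | 5% | 12% | 35% |
| 5 | 0.80 | 5% | 10% | 24% |
| 7 | 1.12 | 5% | 7% | 15% |
| 8 | 1.28 | 5% | 7% | 12% |
| 16.1 (extreme) | 2.57 | 5% | 5% | 7% |

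Without the design factor, the 1 cm column would be 48% at SD 4, 34% at SD 5 and 16% at SD 8. Attrition works the other way: it enlarges the SE and lowers the inflation.

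**The case against.** The strongest objection is that this is a condensed article. Rosters of assessors and recording sheets are normally left to a full protocol or a manual, so silence about them proves nothing. That stands as far as it goes, and masking may be described elsewhere. But the article does fix who measures WC and who trains and supports the intervention sites, and it is the research team in both cases. The point concerns that stated arrangement.

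A second objection is that WC measurement follows a published guideline. This is a real safeguard and limits variation in technique. As described, it does not conceal the arm or the earlier value.

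A third is that the magnitude is hypothetical. This stands. Neither the size of the bias nor the SD of change comes from the article. The calculation shows what a bias would do, not that one exists.

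Several stronger readings are tempting, and the article does not support them:
- *The trainer is the measurer.* The article has one researcher visit every intervention SHO and one of the researchers read the tape. It shows a shared team, not a shared individual.
- *The measurer helped deliver the program.* Study duration and intervention components assigns delivery to the SHOs' own mental health professionals. Researchers instruct those staff and are available to them.
- *The measurer sees the baseline value at follow-up.* This is possible but not stated.
- *WC alone would establish effectiveness.* The article does not say so, and its sample size rests on body weight.

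There is also a caution about the remedy. Baseline is complete, and one person trained all intervention SHOs. Barring that person from follow-up measurement alone could change the observer mainly in the intervention arm, so that a constant offset no longer cancels. Reassignment within the team also leaves the new measurer aware of the arm.

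**Conclusion.** The concern holds in a limited form. WC is a tape-read primary outcome, measured by a team that trains and supports one arm and that, with allocation by site, probably knows which arm it is measuring. That the assessors are unmasked is an inference from these facts, since the article does not discuss masking of assessors.

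A 1 cm shift at follow-up in one arm would raise the WC false-positive rate from 5% to roughly 15-35%, and 0.5 cm would raise it to about 7-12%. Both ranges assume an SD of change of 7 down to 4 cm, baseline numbers without attrition and the plan's design factor of 1.5. Only a shift that differs by arm and arises after baseline has this effect. The argument does not carry over with the same force to weight and fat mass, which the scale reads.

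This is an inexpensive improvement that should be made. It is not evidence that the WC result will be biased, and confidence in its practical size is medium.

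**What to change.** In Primary outcome measures, add for both arms:

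- WC at 10 and 36 weeks is the mean of two readings, recorded on a sheet that does not show earlier values.
- Existing team members are assigned to SHOs in both arms, and the assessor's identity is recorded at each visit.
- The baseline assessor is kept at follow-up where possible. Where that is not possible, changes of assessor are made equally in both arms.
- The researcher who trained the intervention SHOs does not measure there, provided that this does not create a change of observer in one arm only.
- WC is assessed without masking, and a positive result on WC alone will be interpreted with caution alongside scale-measured weight.

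These steps reduce the bias but do not remove it, because the measurer will still usually know the arm. They need a new recording sheet, about one extra minute per patient and less flexible visit planning. They need no additional staff.

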#### Secondary outcome measures

Changes in PA are assessed using the Dutch long version of the self-administered International Physical Activity Questionnaire (IPAQ), as this questionnaire appears to be a reliable and valid PA measurement tool [31]. The analysis of the IPAQ is based on self-reported data. Therefore, PA levels are also measured using pedometers as a more objective tool. The Yamax Digiwalker SW-200 (Yamax, Tokyo, Japan) is used as this is known as accurate and reliable for counting steps [32]. Dietary habits of the participants are assessed using an adapted version for adults of the “Young Children’s Nutrition Assessment on the Web ”[33]. Quality of life is assessed using the SF-36 Health Survey questionnaire. Finally, psychiatric symptom severity is assessed through the use of the Brief Symptom Inventory (BSI). This questionnaire is considered as a reliable and a valid tool useful in patient groups with different psychiatric diagnoses [34].

Data on all primary and secondary outcome measures are collected at baseline and at 10 weeks. At the end of the study (at 36 weeks) only data on body weight, WC and fat mass will be collected and BMI will be calculated. At that time participants will be asked to only complete again the SF-36 Health Survey.

#### Cost-effectiveness

As there is growing need for health economic research in health care and health policy, the cost-effectiveness of the health promotion intervention will also be examined. This will occur by calculating the difference in costs between intervention and no intervention (usual care), by calculating the expected health gain expressed in quality-adjusted life years (QALY) through health economic modeling, and by calculating the Incremental Cost-Effectiveness Ratio (ICER). The ICER is calculated as the ratio of the net cost to the net health gain: ICER = (COST_I_ – COST_NI_)/(QALY_I_ –QALY_NI_) where I is intervention and NI is no intervention.

QALYs are calculated by multiplying the utility level for a given disease status (a health-related quality-of-life weight ranging between 0 and 1) with the number of years an individual suffers from that disease. A utility of 0 is assigned to death, while an utility of 1 represents perfect health.

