## Methods and design

### Aim of the study and hypotheses

The aim of the study is to evaluate the effectiveness and cost-effectiveness of a health promotion intervention targeting PA and healthy eating in people with MD living in sheltered housing. We hypothesize that:

· Between baseline and the end of the intervention and after a 6-month follow up period, significant differences in the primary outcomes ‘body weight’,‘Body Mass Index’ (BMI), ‘waist circumference’ (WC), ‘fat mass’ between the intervention and control group will be identified;

· Between baseline and the end of the intervention and after a 6-month follow up period, significant differences in the secondary outcomes ‘quality of life’ (QOL), ‘PA levels’, ‘eating habits’, and ‘psychiatric symptom severity’ between the intervention and the control group will be identified;

· The health promotion intervention is cost-effective.

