### Data analysis

Parametric and non-parametric tests are used at the individual level to compare the intervention and control group at baseline, depending on the distributions of the quantitative variables. The X²-test is used in qualitative variables. Repeated measure analyses will be used to evaluate differences in the primary outcome variables body weight, BMI, WC and fat mass between pre- and post-intervention in the intervention and control group. Because preference randomization occurred at the level of SHO and not at the level of the individual patient, cluster effects will also be examined. The analyses of the primary outcomes will be performed on an intention to treat (ITT) basis. Secondary outcome variables will be evaluated per protocol. A P-value ≤0.05 is considered statistically significant. For statistical analyses, SPSS®19 will be used.

To examine the cost-effectiveness of the intervention, a Markov decision-analytic model assuming a public payer perspective will be constructed to project health outcomes and costs of the health promotion intervention compared with usual care. Overweight and obesity are substantial risk factors for the high prevalence of type 2 diabetes and cardiovascular disease in individuals with MD[35,36]. Therefore, the Markov model will be used to estimate, for both the intervention and control group, the development of cardiovascular disease and type 2 diabetes over time and the associated costs. The time horizon will be a 10-year period. In both the intervention and control arm several health states will be included in the Markov model. All future costs and health outcomes will be discounted respectively at 3% and 1.5% annually. The costs will be calculated by analyzing the direct health care costs and the costs of the program. The direct health care costs include hospitalization, medication, GP consultations, and other health professionals costs. The program related resource use (staff time, materials) and resulting costs will be calculated making a distinction between the resource used and costs related to the research purpose and those related to the intervention itself.

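### As described, the QALY rests on disease-status utilities in a cardiovascular/diabetes model with no link to the SF-36, so quality-of-life effects not mediated by those diseases would stay outside the ICER unless state utilities differ by arm

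*Protocol article*

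**What the plan says.** The third hypothesis under Aim of the study and hypotheses is "The health promotion intervention is cost-effective". The Cost-effectiveness section obtains the health gain "by calculating the expected health gain expressed in quality-adjusted life years (QALY) through health economic modeling" and divides the net cost by the net QALY gain to give the ICER. It then says how the QALY is formed: "QALYs are calculated by multiplying the utility level for a given disease status", described as "a health-related quality-of-life weight ranging between 0 and 1", "with the number of years an individual suffers from that disease". Death is given 0 and perfect health 1.

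The Data analysis section says that "the Markov model will be used to estimate, for both the intervention and control group, the development of cardiovascular disease and type 2 diabetes", over 10 years, with costs discounted at 3% and health outcomes at 1.5% a year. Programme resource use and its cost are counted. Several health states are announced but not listed, and no source is given for the utility weights.

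Quality of life is a secondary outcome with its own between-group hypothesis. Under Secondary outcome measures it is assessed with the SF-36 at baseline and 10 weeks. It is also the one questionnaire kept at 36 weeks: "At that time participants will be asked to only complete again the SF-36 Health Survey".

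**The concern.** The ICER denominator is the difference in QALYs between intervention and no intervention. If a utility belongs to a disease status, two people in the same state receive the same weight whichever arm they are in. The arms can then differ only through time spent in the modelled disease states.

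The programme consists of group sessions, supervised walking and individual support. The trial itself expects it to change quality of life, and some of that change need not pass through cardiovascular disease or diabetes. On the description given, such a change would be recorded by the SF-36 but would not reach the ICER.

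The distortion could go either way. If the programme improved well-being with little lasting effect on weight, the denominator would be near zero against the full programme cost, and the ICER would look too unfavourable. If the programme lowered well-being, the harm would be missed and the ICER would look too favourable.

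**Working it through.** The article gives no QALY, utility or ICER figure, so there is nothing to reproduce. The check has two parts.

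**1. Following the SF-36 through the text**

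- Hypotheses: quality of life is to differ between groups.
- Secondary outcome measures: the SF-36 is taken at all three assessments.
- Cost-effectiveness: the QALY is utility of a disease status × years with that disease.
- Data analysis: the model follows cardiovascular disease and type 2 diabetes. The SF-36 is not mentioned as an input, and neither is any other utility source.

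The chain stops between the second and third steps.

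**2. Illustrating the size**

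From the article: assessments at 0, 10 and 36 weeks, a 10-year horizon, and 1.5% discounting of health outcomes. Everything else below is assumed.

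*Part not counted.* Let a between-arm utility difference d rise linearly from 0 to its full value at week 10.

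- Held to week 36: d × (10/52/2 + 26/52) = d × 0.596.
- Fading linearly to zero at week 36: d × (10/52/2 + 26/52/2) = d × 0.346.

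| d (assumed) | Held | Fading |
|---|---|---|
| 0.01 | 0.0060 | 0.0035 |
| 0.03 | 0.0179 | 0.0104 |

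The range is therefore about 0.003 to 0.018 QALY per person.

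*Part counted.* Take a two-state annual model (disease-free, diseased) with 10 cycles, half-cycle correction, no deaths, and the same state utilities in both arms. Assume incidence of 1 to 3% a year, a relative reduction of 5 to 10%, and a utility decrement of 0.1 to 0.2.

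| Duration of the effect on incidence | QALY gain, lowest to highest inputs | Mid-range inputs (2%, 7.5%, 0.15) |
|---|---|---|
| 1 year | 0.0004 to 0.0047 | 0.0018 |
| 10 years | about 0.002 to 0.023 | 0.0092 |

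*Check of the mechanism.* A second two-state model, with assumed utilities of 0.85 and 0.70 in both arms and no half-cycle correction, gives:

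- incidence 2.0% in both arms: QALY difference 0.000, whatever happens to well-being within a state;
- incidence 2.0% against 1.9%: 0.0055;
- incidence 2.0% against 1.8%: 0.0111;
- incidence 3.0% against 2.7%: 0.0159.

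Quality of life preserved by avoiding disease is thus counted. A direct effect is not.

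*Overlap if both parts are added.* At the top of the assumed inputs, the between-arm difference in disease by week 36 is 3% × 36/52 × 10% = 0.21%. Times a decrement of 0.2 and an average of half of 36 weeks (0.346 year), this is about 0.00014 QALY. Double counting would be negligible under these assumptions.

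**The case against.** Four arguments weigh against the point.

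- **The text is a short definition in a condensed article.** Health states and utility sources are not listed, and weights that differ by arm or draw on the SF-36 are not ruled out. Keeping the SF-36 at 36 weeks would even fit a planned economic use. This stands in part: equal state utilities are an inference, and the absence of a listed source is no finding in itself. But the QALY rule is printed and ties utility to disease status, and equal weights within a state are its natural reading.
- **A disease model suits a weight intervention.** All four primary outcomes are anthropometric, and the article justifies the model by the link from overweight to diabetes and cardiovascular disease. This stands. The choice limits scope and does not contradict the secondary hypothesis.
- **The sizes are assumed.** This stands. The two ranges overlap, and leaving deaths out of the illustration may understate the counted part.
- **SF-36 utilities bring their own bias.** Participants are unblinded and report on themselves, and 14 + 5 = 19 of 25 organisations chose their arm. Secondary outcomes are also to be analysed per protocol. This stands, and it argues for a sensitivity analysis, not a new base case.

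A reader might infer that the endpoint cannot register any quality-of-life effect. The documents do not support that: utilities are quality-of-life weights, and disease avoided changes the QALYs. Nor do they support saying that the SF-36 has been excluded from the economic evaluation; the article simply does not link the two.

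**Conclusion.** The point holds as a limitation of scope. On the natural reading, quality-of-life effects not mediated by cardiovascular disease or type 2 diabetes would not enter the ICER, while programme costs would. This rests on one assumption: that state utilities are the same in both arms.

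The size is illustrative only. For an assumed utility difference of 0.01 to 0.03, the part left out is about 0.003 to 0.018 QALY over 36 weeks. That is of the same order as the part counted under the assumed disease inputs. It tends to be the larger of the two when the effect on weight is short-lived, but not in every scenario. A reader might conclude that the ICER is wrong by some given factor; without utilities or event rates in the article, no such factor can be stated.

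**What to change.** Keep the disease-based Markov model as the base case. In the Cost-effectiveness and Data analysis sections, or in the economic analysis plan:

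1. State the source of the state utilities and whether they are the same in both arms. If they are, label the base-case ICER as excluding direct quality-of-life effects.
2. Pre-specify a sensitivity analysis that derives SF-6D utilities from the SF-36 at baseline, 10 and 36 weeks. Take the between-arm difference in the 36-week area under the utility curve, adjusted for baseline utility and for clustering by sheltered housing organisation.
3. Run it by intention to treat, and say so explicitly, because the plan otherwise evaluates secondary outcomes per protocol.
4. Add this difference to the first model cycle, and report the ICER with and without it.
5. State beside the result that the component rests on self-report by unblinded participants and that 19 of 25 organisations chose their arm.

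The cost is analysis wording, one scoring step and one additional model run on data already being collected. No new visit or questionnaire is needed. The drawback is the bias risk in item 5, which is why the component belongs beside the base case and should not replace it.
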